**Outcomes**			
*Diagnosis of NPH*	ICD10 code G91.2 or context-confirmed description of diagnosis of NPH in medical record	CRIS or HES or ONS	Medical record
*Dementia diagnosis*	ICD F00-03 diagnosis on or closest after index date	CRIS or HES or ONS	Medical record
*Cognitive trajectory*	All additional recorded MMSE scores at least three months after index MMSE, until censoring occurs	CRIS	Medical record
*All cause mortality*	First date of death recorded after index date	CRIS	Medical record
*Cause of death*	Recorded primary cause of death based on death certificate	ONS	ONS data
*Hospitalisation profile*	Date and diagnosis associated with hospital episode	HES	Medical record

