### Study design

We will assemble a retrospective cohort study using SLaM’s CRIS data platform. The study population will be all people aged 60 years and above with at least one referral to memory services recorded over the study period 2007–2024. We expect at least 20,000 participants in this cohort. We will extract relevant anonymised retrospective patient data from CRIS for the entirety of the cohort and specify the data extraction date. We will examine CRIS data and use linkage data to HES, ONS, and imaging data.

A subset of this cohort will have linked T1-w, T2-w, and FLAIR brain MRI scans that have been collected as part of routine clinical care over the period 2008–2021. We expect to have at least 5,000 people in this sample, based on the number of scans currently available, however the sample size is subject to change as these datasets are live.

*Inclusion criteria:*

Aged at least 60 years at time of memory clinic referralReferral to memory services, recorded in CRISPeople who are referred but do not attend a review will be included and compared with those who do attend, though they may have limited data

*Exclusion criteria:*

Nil

*Cohort entry date:*

Date of referral to memory service

*Exit from cohort:* Censored at minimum of

DeathIncident NPH diagnosisEnd of study period

*Covariate assessment window:*

Anytime prior to cohort entry date up to three months after date of first face-to-face or virtual review in memory clinic, inclusive

*Primary outcome:* ICD10 code G91.2 recorded in CRIS
*or* HES
*or* ONS,
*or* context-confirmed NPH recorded in CRIS

*Possible secondary outcomes:*

MortalityHospitalisation profileDementia diagnosisCognitive trajectorySymptoms of NPH (eg. falls)

*Exposures:*

CA in degreesVentricular volume in mm
^3^
White matter hyperintensities (WMH) volumesOther brain measures to be determined (TBD)

*Possible covariates:*

AgeSexEthnicityIMDRisk factors for NPHCognitionHealth of the Nation Outcome Score (HoNOS)

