### Potential further analyses

Depending on our initial exploratory findings, we will consider additional analyses. If we have sufficient cases of individuals with imaging features of NPH, we plan to undertake additional statistical analyses, such as Cox regression with time to mortality or dementia diagnosis as outcomes.

If we have sufficient cases, we will describe NPH imaging features in relation to outcomes such as hospitalisation, mortality, cognitive decline, and dementia diagnosis. We will describe hospitalisation profiles (eg. falls, surgery) in relation to NPH imaging features. We will look at factors associated with subsequent diagnosis compared to no diagnosis among people with imaging features of NPH.

If, as expected, we find few cases of NPH, we will define NPH ‘imaging cases’ based on the presence of suggestive imaging features and their relationship with NPH diagnosis, and consider a nested case-control study. We will assess for differences in risk factors, demographics, and clinical covariates (see
Table 2) between cases and controls using logistic or categorical regression.

We plan to test our measures in low-field MRI
^
72
^, and we will consider comparing our findings in other datasets
^
73
^.

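### If the Table 2 dementia definition is reused as the event in the optional time-to-dementia Cox model, dementia already present at referral or first assessment is counted as a follow-up event

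*Protocol article*

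**What the plan says.** All references are to the protocol article.

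- **Outcome.** Table 2, Outcomes, defines dementia diagnosis as "ICD F00-03 diagnosis on or closest after index date", from CRIS, HES or ONS. The clinical data text presents Table 2 as the complete definition of the pre-specified variables.
- **Population and entry.** Study design takes "all people aged 60 years and above with at least one referral to memory services recorded over the study period 2007–2024". Cohort entry is "Date of referral to memory service". The entry under "Exclusion criteria" is nil.
- **Exit.** Follow-up ends at death, incident NPH or the end of the study period. Dementia status plays no part, and NPH is the only condition described as incident.
- **Baseline.** The covariate window in Study design runs from any time before entry to three months after the first memory clinic review. The diagnosis covariate in Table 2 is the one nearest the index date.
- **Model.** Potential further analyses states: "If we have sufficient cases of individuals with imaging features of NPH, we plan to undertake additional statistical analyses", and gives as an example "Cox regression with time to mortality or dementia diagnosis as outcomes".
- **Contrast.** Cognitive trajectory in Table 2 uses only MMSE scores at least three months after the index score. Dementia has no such lag.

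**The concern.** A Cox model of time to dementia needs people who are free of dementia when the clock starts. This cohort consists of people referred to memory services, so many may have dementia at referral or receive the diagnosis at the first assessment. With the Table 2 rule as the event and referral as time zero, two groups enter as early events:

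- people whose existing dementia led to the referral, with an event time that reflects the wait for assessment and coding;
- people with dementia recorded before referral, as soon as an F00-03 code is entered again.

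For both groups the event time says little about when dementia began. The Memory services section of the Introduction says the study will ask whether imaging features independently predict outcomes. A hazard ratio from such a model would partly describe who already had dementia when scanned.

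**Working it through.** **No figure to reproduce.** The article states no event count, rate or power for dementia. Its sample-size calculation concerns mean callosal angle in NPH and Alzheimer's dementia and does not bear on this point.

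**Step 1: follow one record through the rules.** A person is referred on day 0 and given an F00-03 code at the first review.

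- The code falls inside the covariate window, which closes three months after that review, and can be the diagnosis nearest the index date. It is then a baseline diagnosis.
- The code is also the first on or after the index date. It is then the dementia outcome.
- No exclusion, lag or exit rule separates the two uses.

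**Step 2: what share of counted events would be later onset?** Let *p* be the share with dementia at baseline, *r* the yearly onset rate in the rest, and *t* the years of follow-up. Ignore death and assume every prevalent case is coded.

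- Later-onset events = N × (1 − p) × (1 − exp(−r t))
- Prevalent events = N × p
- Share = later-onset / (later-onset + prevalent)

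N = 5,000 is the expected imaging subset. The values of *p*, *r* and *t* are assumptions. Scans run from 2008 to 2021 and the study ends in 2024, so potential follow-up from scan is roughly 3 to 16 years.

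| p | r per year | t (years) | Prevalent | Later onset | Share later onset |
|---|---|---|---|---|---|
| 50% | 5% | 4 | 2,500 | 453 | 15% |
| 50% | 10% | 4 | 2,500 | 824 | 25% |
| 20% | 5% | 4 | 1,000 | 725 | 42% |
| 20% | 10% | 4 | 1,000 | 1,319 | 57% |
| 50% | 5% | 9 | 2,500 | 906 | 27% |
| 50% | 10% | 9 | 2,500 | 1,484 | 37% |
| 20% | 5% | 9 | 1,000 | 1,449 | 59% |
| 20% | 10% | 9 | 1,000 | 2,374 | 70% |

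First row: 2,500 × (1 − exp(−0.05 × 4)) = 2,500 × 0.1813 = 453, and 453 / (453 + 2,500) = 15%.

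**Step 3: what happens to the hazard ratio?** A share of events is not a bias, so Cox models were fitted to simulated data. All inputs are assumed: 5,000 people, 25% exposed, onset 0.08 per year in the unexposed, death 0.05 per year, administrative censoring at 1 to 12 years, prevalent cases coded within six months of referral, 10 replicates.

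*True hazard ratio for later onset 1.5, prevalence equal in both groups:*

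| Prevalent share of cohort | Prevalent share of events | HR, everyone | HR, dementia-free at baseline |
|---|---|---|---|
| 20% | 41% | 1.31 | 1.52 |
| 40% | 65% | 1.16 | 1.53 |
| 60% | 80% | 1.10 | 1.48 |

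*True hazard ratio 1.0, prevalent dementia 10 percentage points commoner in the exposed:* using everyone gives 1.21 to 1.24. The dementia-free set gives 0.95 to 0.99, close to 1 given so few replicates.

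The first case dilutes a real association towards 1. The second creates one where there is none.

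**The case against.** **The model is only a possibility.** It sits under potential further analyses, is given as an example and depends on numbers. Dementia is listed among possible secondary outcomes, and Analysis plan calls the study mainly descriptive and exploratory. This stands, and it limits the weight of the point.

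**A risk set is commonly left to the analysis plan, and only an article is shown.** This stands in part. Silence about the risk set would not by itself be a finding. But the outcome definition is stated, is presented as complete, and cannot serve this model as worded.

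**The definition and the nil exclusions have good uses.** This stands. Diagnostic accuracy of CA compares callosal angle between NPH and dementia groups, which needs the diagnosis made around assessment. The Introduction also plans to study prognosis in other diagnoses such as Alzheimer's disease, so people with dementia must stay in the cohort. The fault lies only in reusing the definition as a time-to-event endpoint.

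**Index date is not defined.** Referral is the natural reading but is inferred. If it meant first review or scan, a diagnosis made that day would still count, because the wording includes the date itself. It also stands that dementia known before referral counts only if it is recorded again.

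**Stronger readings that the article does not support.** A reader might infer that the protocol claims to predict incident dementia. It never calls dementia incident, and its explicit prediction hypothesis concerns NPH diagnosis. A reader might also infer that most counted events would necessarily be prevalent dementia. That depends on unstated inputs, and in three of the eight rows above later onset is the majority.

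**Conclusion.** The point holds for one conditional, exploratory analysis. Used as the event in a Cox model timed from referral, the Table 2 definition would count existing and newly assessed dementia as follow-up events, and the resulting hazard ratio could be too low or too high.

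The size cannot be fixed from the article. Under the assumptions above, later onset makes up about 15% to 57% of counted events at four years and about 27% to 70% at nine. In the simulated examples a true hazard ratio of 1.5 fell to between 1.10 and 1.31, and a true 1.0 rose to between 1.21 and 1.24. These figures show direction and order of size; they are not forecasts for this cohort.

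The primary NPH outcome, the period prevalence of NPH and the callosal angle comparison do not use a dementia risk set and are not affected.

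**What to change.** 1. Keep the Table 2 definition for classifying people by diagnosis, and state there which date is the index date.
2. For any time-to-dementia model, restrict the risk set to people with no F00-03 record in any source up to the end of the protocol's own covariate window, three months after first review.
3. Start follow-up at the end of that window, or at the scan if later, since imaging measures are dated to the scan. Where the scan is later, extend the dementia-free condition to the scan date.
4. Analyse dementia at assessment separately, by logistic regression on the imaging features.
5. State how people who never attend a review are handled in this model. The cohort includes them, and for them the window has no end date.

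This takes a line in Table 2 and a few sentences in the analysis section, and no new data. The cost is fewer events in the Cox model and less precision, but the events lost are those that cannot speak to later onset. The three-month cut-off is one choice among several; its merit is that the protocol already uses it.

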**Imaging parameters**			
*CA measure*	Angle between medial walls of lateral ventricles on date of scan, in degrees, measured using algorithm. When measured manually, this will be defined as the angle of the corpus callosum at the level of the posterior commissure, at the plane perpendicular to the anterior commissure-posterior commissure line, by convention ^ 29 ^.	SLaM Image Bank	MATLAB algorithm and manual measurement
*Ventricular volume*	Volume of right and left lateral ventricle in mm ^3^ on date of scan, derived from segmentation data	SLaM Image Bank	SynthSeg output
*White matter hyperintensity (WMH) volumes*	Binary mask of WMH locations and volume measures (mm ^3^). This will be further segmented into periventricular region WMHs.	SLaM Image Bank	WMH-SynthSeg output
*Other imaging features*	Segmentation values for hippocampal, intracranial, extra-ventricular CSF volumes in mm ^3^ on date of scan	SLaM Image Bank	SynthSeg output
*Potential additional features*	EI, z-EI, CSF volume at high convexity region and Sylvian fissures	SLaM Image Bank	Pipelines developed from SynthSeg output

To measure CA, we will extract the ventricles from SynthSeg segmentations. [name]
*et al.*
^
34
^, who originally developed an algorithm calculating CA automatically, are collaborators on this project and have kindly shared their code, developed in MATLAB, for use in this study. This tool is not under copyright and the developers of the tool are co-authors on this protocol. This algorithm calculates the angle between the medial walls of the ventricles to approximate CA. We will test this algorithm in our population and, if necessary, adapt it.

We will run WMH-SynthSeg to automatically assess for WMH using T2-weighted (T2-w) or FLAIR MRIs
^
63
^. WMH-SynthSeg has previously been shown to identify WMHs with high accuracy compared to manual delineation (r=0.84, p < 0.001), even in a cognitively-impaired population, as well as showing a stepwise association with manually-derived Fazekas score
^
64
^. We will validate WMH-SynthSeg output against manual measurements, and undertake visual quality control assessment of both T2-w or FLAIR images and WMH-SynthSeg output.

WMHs are a recognised feature of NPH and we will include these as part of the Kockum Radscale. We will investigate the association between WMHs and other measures such as ventricular volume and CA. We will consider the additive effect of these markers when combined in analyses, compared to when they are examined individually.

We will aim to develop other automated measures of NPH imaging biomarkers such as EI, z-EI
^
65
^, and CSF volumes at the high convexity and Sylvian fissures
^
66
^. These will be compared with manual measurements by SI and [name].

**
*Clinical data.*
** We will work with the CRIS team to extract clinical data and, where necessary, link this to available images via patients’ Maudsley Biomedical Research Centre identification codes. We will use a combination of structured and unstructured field searches, depending on the variable of interest. We will use natural-language programming (NLP) applications available via the CRIS catalogue
^
67
^ to characterise symptoms, diagnoses, comorbidities, and risk factors. At present, there is no NLP application to assess gait in CRIS.

Pre-specified variables of interest are fully defined in

### Study design

We will assemble a retrospective cohort study using SLaM’s CRIS data platform. The study population will be all people aged 60 years and above with at least one referral to memory services recorded over the study period 2007–2024. We expect at least 20,000 participants in this cohort. We will extract relevant anonymised retrospective patient data from CRIS for the entirety of the cohort and specify the data extraction date. We will examine CRIS data and use linkage data to HES, ONS, and imaging data.

A subset of this cohort will have linked T1-w, T2-w, and FLAIR brain MRI scans that have been collected as part of routine clinical care over the period 2008–2021. We expect to have at least 5,000 people in this sample, based on the number of scans currently available, however the sample size is subject to change as these datasets are live.

*Inclusion criteria:*

Aged at least 60 years at time of memory clinic referralReferral to memory services, recorded in CRISPeople who are referred but do not attend a review will be included and compared with those who do attend, though they may have limited data

*Exclusion criteria:*

Nil

*Cohort entry date:*

Date of referral to memory service

*Exit from cohort:* Censored at minimum of

DeathIncident NPH diagnosisEnd of study period

*Covariate assessment window:*

Anytime prior to cohort entry date up to three months after date of first face-to-face or virtual review in memory clinic, inclusive

*Primary outcome:* ICD10 code G91.2 recorded in CRIS
*or* HES
*or* ONS,
*or* context-confirmed NPH recorded in CRIS

*Possible secondary outcomes:*

MortalityHospitalisation profileDementia diagnosisCognitive trajectorySymptoms of NPH (eg. falls)

*Exposures:*

CA in degreesVentricular volume in mm
^3^
White matter hyperintensities (WMH) volumesOther brain measures to be determined (TBD)

*Possible covariates:*

AgeSexEthnicityIMDRisk factors for NPHCognitionHealth of the Nation Outcome Score (HoNOS)

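### The single exit rule censors at incident NPH diagnosis without limiting this to the NPH-diagnosis outcome, and it conflicts with Table 2 and with the aim of describing outcomes of NPH

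*Protocol article*

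**What the plan says.** Under Exit from cohort, the Study design section has a single rule: "Censored at minimum of" three items, "DeathIncident NPH diagnosisEnd of study period" (list items run together in the extracted text). The rule stands before both the primary and the secondary outcomes and is tied to neither. No other end of follow-up appears in the article.

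The possible secondary outcomes in the same section are mortality, hospitalisation profile, dementia diagnosis, cognitive trajectory and symptoms of NPH. The Clinical data text is firmer and says that secondary outcomes will include dementia, mortality, cognitive trajectory, cause of death and hospitalisation.

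The Outcomes rows of Table 2 treat them differently:
- Cognitive trajectory: "All additional recorded MMSE scores at least three months after index MMSE, until censoring occurs".
- All-cause mortality: "First date of death recorded after index date".
- Dementia: "ICD F00-03 diagnosis on or closest after index date".
- Hospitalisation: date and diagnosis of the hospital episode, with no end point.

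Potential further analyses considers "Cox regression with time to mortality or dementia diagnosis as outcomes" and adds: "We will describe hospitalisation profiles (eg. falls, surgery) in relation to NPH imaging features". Neither has its own exit rule.

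**The concern.** Exit at NPH diagnosis suits one outcome, the diagnosis itself, where it is the event. Written for the whole cohort, the rule has two consequences.

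First, an incident case has no follow-up after diagnosis. Aims and objectives sets out to relate recorded NPH, as well as imaging features, to outcomes. Patient and Public Involvement says that questions on outcomes of NPH were added after focus groups. Under the rule, outcomes after diagnosis would be visible only in people diagnosed before referral, who are a selected group.

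Second, in models of imaging features against mortality, dementia, hospitalisation or cognition, the censoring would be informative. The protocol hypothesises that imaging features predict NPH diagnosis, and its Memory services section says that untreated NPH carries a higher risk of dementia and death. Leaving follow-up would thus depend on both exposure and prognosis.

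The conflict with Table 2 also leaves the choice of follow-up open until the data have been seen.

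**Working it through.** The plan states no figure on this point. The check sets the sections side by side and then gauges the size.

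**Text, outcome by outcome**

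| Outcome | Exit rule in Study design | Table 2 | Result |
|---|---|---|---|
| NPH diagnosis | diagnosis listed as censoring | no end point | right time to stop, but it is the event |
| MMSE trajectory | stops at diagnosis | stops at censoring | later scores excluded in both places |
| Death | stops at diagnosis; death also listed as censoring | first death after index date | conflict |
| Dementia | stops at diagnosis | on or closest after index date | conflict |
| Hospital episodes | stops at diagnosis | no stop | conflict |

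Only an incident diagnosis triggers exit. There are no exclusion criteria, so people with NPH recorded before referral stay in follow-up.

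**How many people**

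Inputs from the article: expected prevalence 1%, cohort at least 20,000, imaging subset at least 5,000.
- 0.01 × 20,000 = 200
- 0.01 × 5,000 = 50

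These are upper limits at that prevalence, because cases recorded before entry are not cut.

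**How much of their follow-up (assumed inputs, not in the article)**

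Diagnosis uniform over the first 1, 3 or 5 years; death rate 8%, 12% or 20% a year; administrative follow-up uniform over 0 to 18 years. Share of person-time lost = sum of (end − diagnosis) ÷ sum of end, over those diagnosed before their end of follow-up.
- Lowest: 5 years and 20% a year give 64%. Highest: 1 year and 8% a year give 92%.
- Share of incident cases who die in the study after diagnosis: 43% (5 years, 8%) to 72% (1 year, 20%).

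**Effect on an imaging-feature model (assumed inputs)**

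5,000 scanned, 50 with NPH, base mortality 10% a year doubled by NPH, mean 1.5 years to diagnosis, 3 to 16 years of follow-up. Narrow callosal angle occurs in 97% of NPH and 12% of others, from the sensitivity and specificity in Table 3. Cox model for death on narrow angle:

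| | Full follow-up | Censored at NPH diagnosis |
|---|---|---|
| Deaths among people with NPH | 41.0 | 11.6 |
| Hazard ratio, narrow angle | 1.057 | 1.019 |

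- Deaths lost: 41.0 − 11.6 = 29.4. That is 29.4 ÷ 41.0 = 72% of NPH deaths, but 29.4 ÷ 2,930 = 1.0% of all deaths.
- Shift in log hazard ratio: ln 1.057 − ln 1.019 = 0.055 − 0.019 = 0.037.
- Standard error of the log hazard ratio: about 0.055, so the shift is 0.037 ÷ 0.055 = 0.7 standard errors.
- Entering NPH diagnosis as a time-dependent covariate instead gave the same log hazard ratio for angle as censoring at diagnosis (difference 0.001).

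**The case against.** The strongest reply is that the list was written for the primary outcome. Death appears in it as censoring although mortality is itself an outcome, which suggests as much, and stopping at NPH diagnosis is then correct. Three neighbouring rows of Table 2 have no stop at censoring. The affected analyses are conditional on numbers, the study calls itself mainly descriptive and exploratory, and outcome-specific censoring is often left to an analysis plan.

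Much of this stands. A reader might infer that the rule ends follow-up for every outcome, so that later deaths, dementia and hospital episodes can never be counted. The article does not support that: for these outcomes it is inconsistent, not firmly exclusive, and prevalent cases keep their follow-up. A reader might also infer that shunt admissions would vanish. Shunt surgery is not a named outcome, surgery is only an example within hospitalisation profiles, and an NPH code in the hospital data can itself be the first record of the diagnosis.

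Nor is a bias toward no association established throughout. Only mortality was simulated, with NPH doubling the risk whatever the treatment. The article says treatment is beneficial; if shunting lowers risk, removing time after diagnosis could strengthen an association.

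What does not fall away is that the rule is stated without limit, Table 2 applies it outright to MMSE, and the Clinical data text says that these secondary outcomes will be included. This is a stated rule, not a detail left for later.

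**Conclusion.** The point holds as a conflict within the protocol and a badly fixed exit rule. MMSE scores after an incident NPH diagnosis are excluded outright; for death, dementia and hospital episodes, Study design and Table 2 disagree. Followed literally, the rule prevents any description of outcomes after an incident diagnosis and makes censoring informative in the imaging-feature models.

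The size differs by question. For outcomes after an incident NPH diagnosis the loss is total by construction. For an overall hazard ratio the effect is probably small: at most about 1% of people are touched, and the illustrated shift is 0.7 of a standard error. That figure rests on assumed death rates, time to diagnosis and follow-up, and the direction is not established for every outcome. The stronger claim, that the prognosis question as a whole cannot be answered, goes too far, because about 99% of the scanned sample is untouched and the article also asks about prognosis in other diagnoses. Prevalence, the comparison of callosal angle between diagnoses, and the logistic regression are unaffected.

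**What to change.** Replace the single list with an end of follow-up for each outcome:
- **NPH diagnosis:** diagnosis is the event, death a competing event, end of study the censoring.
- **Mortality:** death is the event; censor only at end of study.
- **Dementia:** follow to dementia diagnosis, death or end of study, whichever is first.
- **Hospitalisation and MMSE:** follow to death or end of study.

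In the main imaging-feature models, neither censor at NPH diagnosis nor adjust for it. Diagnosis lies between the imaging feature and the outcome, and adjusting for it gave the same result as censoring. Keep censoring at diagnosis as a stated sensitivity analysis, and use a time-varying NPH state only where the question is the outcome after diagnosis. Reword the MMSE row of Table 2 to match, and reconcile the other outcome rows with Study design.

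The cost is wording. The article already plans extraction for the entire cohort with hospital and mortality linkage, so no new data source is needed.
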